#### Comparison group

The unexposed represents the counterfactual and will include patients without an SMI Read code ever (hereafter *unexposed*) drawn from the source population. Up to four unexposed matches will be selected at baseline only if they have a qualifying weight Read code within±one year of the index date to the exposed in which they are matched. The matching variables include: age, sex, practice and calendar time. All weight Read codes will be extracted.

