### Confounding

We have identified confounding variables using directed acyclic graphs (DAGs), which aims to theoretically formalise potential confounders, colliders and biasing relationships.^26^ The DAG for each objective is described in online supplemental material S1. The DAG for objective 1 shows one direct path from the exposure (ie, SMI) to the outcome (ie, weight change), and four indirect paths: via health behaviours (ie, alcohol use, smoking and diet), SES status, psychotropic medication, and healthcare access and provision. Diet and physical activity are latent variables in CPRD Aurum because they are unmeasured. There are three confounding paths: via age, sex and ethnicity.^27 28^ Thus, the minimally sufficient adjustment for the total effect of SMI status on weight is to adjust for age, sex, and ethnicity.

10.1136/bmjopen-2021-053427.supp1Supplementary data

Frequency matching will ensure our ability to adjust for confounding variables that include age, sex, and calendar year, and matching on practice will remove practice-specific variables. In addition, we will fully adjust our models by considering several covariates in the relationship between the exposure and outcome (see table 2). All categorical variables will be analysed using the natural reference category as the reference group. Data on individual prescriptions for psychotropic and cardio-metabolic medications will be extracted from the primary care data from index date until censoring. For psychotropic medications, drugs will be classified according to the British National Formulary. For objectives 2 and 3, we will assess the impact of weight gain on change in cardio-metabolic risk factors and incidence of CVD using mediation analysis to allow us to estimate the direct (unmediated) and indirect (mediated) effects of SMI on CVD risk and incidence. To do this, we will fit two regression models: one regressing the outcome on the exposure, adjusting for confounders and another regressing the mediator on the exposure and confounders using the Stata *Med4way* command to estimate mediated effects.^29^ For objective 4, we will assess the presence of confounding by comparing estimates with and without adjustment. We will use Read codes, which have been previously developed by our team, to identify outcome and covariate records.

**Table 2 T2:** Confounders

Confounders and covariates		Measures

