#### Descriptive summaries

Frequency matching will reduce potential confounding and balance the baseline characteristics of the *exposed* and *unexposed* on age, sex, practice and calendar year. Adequacy of matching will be confirmed by comparing means using independent t-tests. Descriptive statistics will describe the baseline characteristics of patients in the cohort. Categorical data will be presented as frequency and percentages, and continuous variables will be summarised using descriptive statistics mean, standard deviation (SD) or median and interquartile range (IQR). Comparisons between the groups will be made using χ^2^ tests and t-tests (or Wilcoxon rank-sum tests) as appropriate. Length of exposure and the most commonly prescribed class of psychotropic for each patient will be summarised. The causes of death will be categorised as CVD and all-cause mortality.

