#### Primary analyses

For objectives 1 and 2, the outcome will be visually inspected by plotting trajectories of weight and cardio-metabolic risk factor change using all repeated measurements for patients with SMI versus patients without SMI. For these analyses, we will use a mixed-effects linear regression model including terms for SMI, time and their interaction to estimate regression coefficients with 95% CIs by SMI status. Models incorporating psychotropic medications will analogously include medication-time multiplicative interaction terms. We will include a random effect for individual and practice identifier to account for intra-class correlation resulting from common practice membership. Diagnostic tests will be conducted to confirm linear regression assumptions are met including linearity of residuals, residual normality using quantile–quantile (Q–Q) plots, and residual heteroscedasticity using residual versus fitted value plots. We will assess for exploratory subgroup effects by adding interactions (eg, by age, sex, ethnicity and SES) and, if significant, we will assess the strength of the associations in separate subgroups for clarity. For objective 2, we will model the association between weight and cardio-metabolic change using restricted cubic splines to allow for non-linear associations. For objective 3, we will use Kaplan-Meier survival estimates for the exposed and unexposed groups to estimate the distribution of time from index date to total and fatal CVD and mortality (all-cause). The statistical equivalence of the two curves will be examined using the log-rank test. This analysis will use a survival from index date between the exposed and unexposed groups using an adjusted Cox proportional hazards regression model with follow-up time as the timescale. Restricted cubic splines will be computed with five knots to visually explore non-linear associations between the exposure and the outcomes. For objective 4, we will use a Poisson regression examining person-time to estimate the rate at which patients who received weight management services over the study period in patients with SMI compared with patients who do not have SMI, adjusting for confounders and BMI.

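### Matching on practice with a variable number of controls does not by itself remove practice effects from the log-rank, Cox and Poisson analyses

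*Protocol article*

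**What the plan says.** **How controls are chosen.** Under Comparison group: "Up to four unexposed matches will be selected at baseline only if they have a qualifying weight Read code" within a year either side of the index date of the exposed patient to whom they are matched. "The matching variables include: age, sex, practice and calendar time". This describes matching to an individual, with a variable number of controls.

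**What the matching is called and said to do.** Descriptive summaries: "Frequency matching will reduce potential confounding and balance the baseline characteristics" on age, sex, practice and calendar year. The Confounding section also speaks of frequency matching and adds, without condition, that "matching on practice will remove practice-specific variables".

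**How practice enters the analyses (Primary analyses).**
- Objectives 1 and 2, mixed models: "We will include a random effect for individual and practice identifier to account for intra-class correlation resulting from common practice membership".
- Objective 3, test: "The statistical equivalence of the two curves will be examined using the log-rank test". No strata are stated.
- Objective 3, model: "using an adjusted Cox proportional hazards regression model with follow-up time as the timescale". No stratum, frailty or cluster term is stated.
- Objective 4: Poisson regression on person-time, adjusted for confounders and BMI. No practice or matched-set term is stated.

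**Covariates.** Table 2 lists age, sex, ethnicity and a practice-level deprivation quintile, among others. It lists neither practice nor calendar year.

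**Objective 4 entry.** An exposed patient joins the subcohort on a BMI of at least 25 kg/m² recorded at any time after the index date, so after matching (Study cohort).

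**The concern.** In a matched cohort analysed by pooling, matching balances a factor only if the ratio of unexposed to exposed is the same at every level of that factor. With an upper limit of four and eligibility tied to weight recording, practices or years that record weight less often can supply fewer controls. The pooled unexposed group then over-represents the practices with more controls, and the exposed group does not. If those practices also differ in CVD coding or in referral, part of the SMI contrast is a contrast between practices.

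Objective 4 is most exposed. Its BMI entry rule acts after matching, so the ratio can change within practices even if it began at 1:4.

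The planned checks would not show the problem. Adequacy of matching is judged by t-tests on means, and practice is a nominal variable with no mean. For objective 4, confounding is judged by comparing estimates with and without adjustment, which cannot reveal confounding by a factor outside the adjustment set.

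**Working it through.** **1. The plan's own figure.** The Sample size calculation uses 3% CVD risk in the unexposed, a relative risk of 1.3 (so 3.9% in the exposed), an n ratio of 0.25 and 80% power. With two-sided alpha 0.05 and pooled variance:
- average risk = (0.03 + 0.25 × 0.039)/1.25 = 0.0318
- unexposed n = [1.960 × √(0.0318 × 0.9682 × 5) + 0.842 × √(0.03 × 0.97 + 0.039 × 0.961/0.25)]² / 0.009² = 15,628
- exposed n = 15,628/4 = 3,907

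The printed 3,907 is reproduced as the exposed group. The calculation assumes a fixed 1:4 ratio. With 135,870 patients with SMI reported as available, power is not at issue. A larger sample only narrows the interval around whatever value the estimator targets.

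**2. Inputs the protocol does not give.** It reports neither the distribution of controls per exposed patient nor the spread of CVD or referral rates between practices. Everything below rests on assumed values and shows a range, not a prediction.

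**3. Referral, no SMI effect.** Half the exposed are in each of two practice types, with rates a and b per 1000 person-years and k and m controls per exposed patient. Exposed rate = (a + b)/2. Pooled unexposed rate = (k·a + m·b)/(k + m).

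| a, b | k, m | Exposed | Unexposed | Ratio |
|---|---|---|---|---|
| 30, 15 | 4, 2 | 22.5 | (120 + 30)/6 = 25.0 | 0.90 |
| 24, 16 | 4, 2 | 20.0 | (96 + 32)/6 = 21.3 | 0.94 |
| 30, 15 | 4, 1 | 22.5 | (120 + 15)/5 = 27.0 | 0.83 |
| 30, 15 | 2, 4 | 22.5 | (60 + 60)/6 = 20.0 | 1.125 |

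The last row swaps the controls of the first, and the bias reverses.

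**4. CVD, true ratio 1.30.** Low-risk practices have rate 1 and k controls; high-risk practices have rate r and m controls. Pooled ratio = [1.3 × (1 + r)/2] / [(k + m·r)/(k + m)].

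| k, m | r = 1.2 | r = 1.5 | r = 2.0 |
|---|---|---|---|
| 4, 4 | 1.300 | 1.300 | 1.300 |
| 4, 3 | 1.317 | 1.338 | 1.365 |
| 4, 2 | 1.341 | 1.393 | 1.463 |

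Example (4, 2, r = 1.5): 1.625 / (7/6) = 1.393.

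**5. Simulation.** Assumed: 200 practices, about 41 exposed each, 4.6 years, 1% per year, about three controls per exposed patient on average, true ratio 1.30, 1000 data sets per setting. Rate ratios with constant rates stand in for Cox and Poisson. The second column is the fall in controls per exposed patient for each SD of practice log-rate.

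| SD of practice log-rate | Fall in controls | Pooled ratio | Model SE / true SE | 95% CI coverage |
|---|---|---|---|---|
| 0.2 | 0 | 1.299 | 0.0536 / 0.0542 | 95% |
| 0.2 | 0.3 | 1.322 | 0.0538 / 0.0539 | 94% |
| 0.2 | 0.6 | 1.351 | 0.0539 / 0.0533 | 89% |
| 0.2 | 1.0 | 1.375 | 0.0542 / 0.0549 | 82% |
| 0.4 | 0 | 1.301 | 0.0519 / 0.0516 | 95% |
| 0.4 | 0.3 | 1.355 | 0.0522 / 0.0517 | 87% |
| 0.4 | 0.6 | 1.411 | 0.0526 / 0.0523 | 64% |
| 0.4 | 1.0 | 1.468 | 0.0533 / 0.0563 | 38% |

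Practice-stratified estimates stayed between 1.295 and 1.303 in every setting, with coverage of 94 to 96%. When the number of controls varied independently of practice risk, the pooled estimate was unbiased.

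**The case against.** **The bias is conditional.** It needs controls per exposed patient both to vary and to move with practice outcome rates. A reader might infer that practice confounding is certain to return. The documents do not support that: they show a variable ratio and a plausible mechanism, but no dependence on practice rates, and nothing in them says that referral is strongly practice-driven. This objection stands and limits the point.

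**The standard errors hold up.** A reader might also infer that the confidence intervals are wrong merely because practice is left out. The simulation does not support this: model-based standard errors were within about 5% of the true ones, and coverage fell because the estimate moved. This stands too.

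**The models are adjusted.** Age and sex are in Table 2, so imbalance on them is handled, and the practice-level deprivation quintile may absorb part of a practice effect. The Confounding section also names calendar year among the factors that matching makes it possible to adjust for, so adjustment may be intended. This stands in part. Calendar year is not in Table 2. The Data linkage section assigns deprivation to descriptive and secondary analyses. The log-rank test carries no adjustment. Practice itself is treated as already removed by the matching.

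**The article is condensed.** Strata or cluster terms may be set out in a fuller plan that is not shown, so silence alone would be no finding. The point rests instead on the unqualified statement about practice, on the contrast with the practice term written for objectives 1 and 2, and on the conflict between individual and frequency matching. A fuller plan would not make those statements correct.

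**Conclusion.** The point holds in a limited form. Given a variable ratio, the statement that matching on practice removes practice-specific variables does not follow for the pooled log-rank, Cox and Poisson analyses as described, and balance on calendar year is not guaranteed either. The two descriptions of the matching also conflict.

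The size is unknown. Under the assumed inputs, a null referral ratio reads 0.83 to 0.94, or above 1 if the pattern reverses. A true CVD ratio of 1.30 reads about 1.32 to 1.46 in the two-type calculation, and up to 1.47 in the simulation. It is unbiased if the number of controls is unrelated to practice rates, and the direction cannot be fixed in advance. These figures leave out covariate adjustment, which may reduce them.

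**What to change.** - State once whether matching is individual or frequency matching, and use that term throughout.
- Objective 3: stratify the log-rank test and the Cox model by practice, with age, sex and calendar year as covariates in the Cox model. Stratifying by matched set is an alternative only if matching is individual and the sets remain intact.
- Objective 4: condition the Poisson model on practice and adjust it for calendar year. Practice is safer than matched set here, because the BMI rule can break sets.
- Report the distribution of controls per exposed patient, so that readers can see whether the ratio varies.
- Qualify the sentence in the Confounding section: practice is controlled by matching together with an analysis that conditions on it.

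The cost is a change of wording and model specification, with no new data. Strata that lack exposed or unexposed patients contribute nothing to the SMI contrast, so some precision is lost. How much cannot be worked out from the protocol.

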Since obesity is modifiable, US and UK clinical guidelines recommend intervening to prevent and manage obesity. In the UK, the first-line intervention is general practitioner (GP) advice or a referral to a weight management programme to support an energy-restricted diet and increase physical activity for people with a BMI >25 kg/m^2^.^16 17^ In the general population, trials of such programmes lead to greater weight-loss than self-directed attempts.^18^ Another study in the general population reported the rates of referral between 2005 and 2012 was 20.0 (95% CI 19.3 to 20.8) per 1000 person-years, compared with weight-related advice at 30.3 (29.3 to 31.4).^19^ This rate is low, and although these interventions may not be recorded, other evidence also point to low rates of intervention.^20^ However, we have no data on whether GPs are using the annual review of people with SMI, which focuses specifically on preventative healthcare, to provide support for weight management such as referrals to weight management programme.

We have been unable to find studies that have followed people with SMI over several years to examine how weight and cardio-metabolic profiles change. It is possible these relate to ongoing psychotropic and/or weight management programmes. The longest study to date was an 18-month trial of people with schizophrenia. In this study, participants randomised to olanzapine had greater increases in weight, glycaemia and adverse lipid profile than other antipsychotics.^21^ Randomised controlled trials (RCTs) are often limited to short follow-up of selected populations, and there are methodological issues surrounding imputation strategies used to address high dropout rates.^22 23^ Thus, it remains unclear how much weight and cardio-metabolic profiles change over the longer term, and how much of the excess incidence and mortality from CVD is explained by those changes in people with SMI.

In this protocol, we outline our plans to address this gap in a large, retrospective, population-based study in people with SMI matched with controls without SMI in the UK from 1998 to 2020. Our objectives are to:

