#### Study cohort

We will select a study cohort from the CPRD Aurum to investigate objectives 1–3. We will identify and extract the records in the primary care and HES dataset for all patients with a diagnosis of SMI (hereafter *exposed*) and who are eligible for data linkage. Diagnostic Read codes, which are the standard clinical codes used in UK general practice, will be used to identify an SMI diagnosis. We will also use codes according to the International Classification of Diseases version 10 (ICD-10) from the HES data. The date of the first SMI Read code will be used as the index date, which is the earliest date that an exposed patient may enter the study. From the study cohort, a subcohort of patients will be selected to investigate objective 4. To enter the subcohort, the exposed patient needs a recorded BMI ≥25 kg/m^2^ at any time after the index date. All information will be extracted for the period 01 January 1998 to 31 October 2020—the earliest and latest dates respectively that data are available.

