Health behaviours	Smoking status	Categorical (0=never; 1=ex-smoker; 2=current smoker (light: 1–9 cigarettes/day; moderate: 10–19 cigarettes/day; heavy: 20+ cigarettes/day)). This is coded in GP records. We will use the most recent recorded value of smoking status at the study start date.
	Alcohol use	Continuous (units per week). This is coded in GP records. We will use the most recent recorded value of alcohol use at the study start date.
Demographics	Socioeconomic status (SES)*	Categorical (quintiles)
	Ethnicity†	Categorical (white; Asian or Asian British; black or black British; other ethnic group, mixed)
	Sex†	Binary (0=male; 1=female)
	Age at study entry, in years	Continuous
Physical and/or medical factors	Baseline weight status (body mass index (BMI))	Categorical (normal weight (BMI 18.5–24.9 kg/m^2^); overweight (25.0–29.9); obese (30.0–34.9); severe obesity (35.0–35.9); morbid obesity (40.0–44.9)
	Psychotropic medication	Categorical (antipsychotics (first-generation and second-generation); antidepressants; mood stabilisers)
	Cardio-metabolic medication	Categorical (blood glucose lowering medications; antihypertensive treatments, statins)
We include the following additional variables for objectives 3 and 4 only		
CVD risk factors	Total cholesterol/HDL ratio	Continuous
	Systolic and diastolic blood pressure	Continuous
	Glycaemia	HbA1c/fasting blood glucose (FBG)

*This variable is grouped according to practice level Index of Multiple Deprivation. This is an indicator of material deprivation based on income; employment; health deprivation and disability; education, skills and training; crime; barriers to housing and services; and living environment. It is categorised as quintiles 1–5 with 1 being the most deprived and 5 being the least deprived.

†This variable is grouped according to recommendations by the UK Office for National Statistics.^33 34^

CVD, cardiovascular disease; GP, general practitioner; HbA1c, haemoglobin A1c; HDL, high-density lipoprotein.

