### Sample size calculation

The estimated median follow-up time for the *exposed* with a weight Read code in their record in the 1 year *before* the index date is 3.2 years (mean: 4.6), which is based on our feasibility work for this project. We assumed a 1% annual incidence rate of CVD meaning 3% of the study population would develop CVD over the 3.2 years of follow-up.^30^ We also assumed a relative risk (RR) of 1.3 for CVD in the *exposed* versus *unexposed*.^31^ The n ratio was set at 0.25, which achieved the best balance between statistical power and data cost. Our calculation suggested a minimum sample size of n=3907 at 80% power to detect an RR of 1.3, alpha <0.05%. Our feasibility estimates indicate that there are 135 870 patients with SMI in CPRD Aurum, meaning the study is sufficiently powered to detect small effects.

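### Objective 4's Poisson model names no term for calendar period or time since entry, and matching balances calendar time only at index, so the SMI rate ratio can be biased if follow-up or subcohort entry differs between groups

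*Protocol article*

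**What the plan says.** Under Primary analyses, objective 4 gets one model: "we will use a Poisson regression examining person-time to estimate the rate at which patients who received weight management services over the study period", "adjusting for confounders and BMI". The same section is explicit about time for the other objectives. Objectives 1 and 2 have a time term and its interaction with SMI, and objective 3 is a Cox model on follow-up time.

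The plan handles calendar time by matching. Comparison group says: "The matching variables include: age, sex, practice and calendar time". Confounding adds: "Frequency matching will ensure our ability to adjust for confounding variables that include age, sex, and calendar year". Table 2 then lists covariates. It includes "Age at study entry, in years", which is also a matching variable, but neither calendar year nor time since entry.

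The objective 4 population is a subcohort. Study cohort says "the exposed patient needs a recorded BMI ≥25 kg/m^2^ at any time after the index date". It gives no matching rule for the unexposed. Statistical analysis sets entry at the index date for all analyses. Extraction runs from 1 January 1998 to 31 October 2020, and follow-up can last up to 22 years.

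**The concern.** A Cox model absorbs variation with time since index in its baseline hazard. A person-time Poisson model does so only if time bands are included. Matching equalises calendar time on the day of entry. It does not equalise it later if one group is followed for longer, nor within a subset selected afterwards on a variable that was not matched.

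Unequal follow-up is plausible on the plan's own premises: shorter life expectancy in SMI (Introduction), and loss through death or leaving the practice (Duration of follow-up). Clustering of weight-related coding near entry is also plausible. Controls must have a weight code within a year of the index date, and Comparison group states no such rule for the exposed.

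The comparison could then partly reflect when each group was observed. With this much data, an error of several per cent could look statistically firm.

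**Working it through.** The plan states no rate ratio or sample size for objective 4, so there is no figure of its own to reproduce here. Its n=3907 is for CVD.

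**Inputs from the documents.** Calendar window T = 22.8 years. Mean exposed follow-up 4.6 years (Sample size calculation; for exposed patients with a weight code in the year before index, not for the subcohort). General-population referral rate 20.0 per 1000 person-years, 2005 to 2012 (Introduction). 135 870 SMI patients.

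**Assumed.** The true SMI rate ratio is 1.00 at every calendar time and every time since entry. Index dates are uniform over the window and identical in both groups. Follow-up is exponential with mean m, cut at the data end, with m = 4.6 for the exposed and 4.6, 5.5, 6.9 or 9.2 for the unexposed. The ratios of m are 5.5/4.6 = 1.2, 6.9/4.6 = 1.5 and 9.2/4.6 = 2. After the cut, mean follow-up is m − (m²/T)(1 − e^(−T/m)) = 3.68, 4.19, 4.89 and 5.80 years, so the realised ratios are 1.14, 1.33 and 1.58.

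**Formula.** Person-time at time t since entry has weight w(t) = e^(−t/m)(T − t)/T. A group's expected crude rate is the w-weighted average of the rate. The table gives exposed over unexposed.

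*First-year clustering.* If the first-year rate is k times the later rate, a group's crude rate is proportional to 1 + (k − 1)p, where p is the share of its person-time in year 1. For m = 4.6, 5.5, 6.9 and 9.2, p = 0.239, 0.213, 0.186 and 0.160. For m = 9.2:
- k = 2: 1.239/1.160 = 1.068
- k = 3: 1.478/1.320 = 1.120

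*Calendar trend.* At time t since entry, calendar time is uniform between t and T, so longer follow-up pushes person-time later. Its mean position is 13.1, 13.4, 13.6 and 13.9 years after the start of 1998.

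| Unexposed m | +5%/year | +10%/year | Year 1 doubled | Year 1 tripled |
|---|---|---|---|---|
| 4.6 | 1.000 | 1.000 | 1.000 | 1.000 |
| 5.5 | 0.991 | 0.984 | 1.021 | 1.036 |
| 6.9 | 0.979 | 0.964 | 1.045 | 1.077 |
| 9.2 | 0.966 | 0.940 | 1.068 | 1.120 |

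*Both at once.* The two effects oppose each other. Multiplying the calendar and first-year rates in the same integral, with unequal follow-up, gives 1.005 to 1.085.

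**If time zero differs.** Suppose exposed time starts at a qualifying BMI 1, 2 or 3 years after index and unexposed time starts at index, both with m = 4.6. The null ratio is then 1.02, 1.04 or 1.06 at +5% a year, and 1.03, 1.07 or 1.10 at +10% a year. If the first year after index carries a doubled or tripled rate, the exposed skip it and the ratio is 1/1.239 = 0.81 or 1/1.478 = 0.68. The documents do not state this reading. They leave it open.

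**Precision.** Assume half of the SMI patients qualify: 135 870 × 0.5 × 4.6 × 0.020 = 6250 exposed events. At 1:4 (Sample size calculation: "The n ratio was set at 0.25") and equal follow-up there are 25 000 unexposed events. The standard error of the log ratio is √(1/6250 + 1/25 000) = 0.0141, so the 95% interval is about ±3%. If a quarter qualify it is about ±4%. The larger errors in the table would exclude 1.00.

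**The case against.** A reader might infer that the plan ignores calendar year, fits one constant rate over 22 years, and so yields a confounded ratio. The text does not support that. Calendar year is matched and is named as a confounder. Objective 4 adjusts for confounders without limiting them to Table 2, and that table is introduced as an addition to the matched factors. A constant rate is nowhere stated, and Poisson regression is compatible with split records. Banding is also a detail that an article may leave to a fuller plan.

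The sizes are open to challenge too. They come from crude rates under assumed trends and assumed control follow-up, while the plan is an adjusted model. The 4.6 years does not describe the subcohort, and the two time effects partly cancel.

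A further inference would be that a pooled ratio defeats the objective, because the Introduction says "we have no data on whether GPs are using the annual review of people with SMI". But objective 4 asks only for a comparison of incidence, which a pooled ratio provides. Period-specific ratios would not show that a referral came from an annual review either.

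All of this stands against the strong reading. It does not remove two facts. The section specifies time for three objectives and not for the fourth, and matching at index does not carry over to later person-time or to a subcohort selected after index.

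**Conclusion.** The point holds as a specification weakness, not as demonstrated confounding. Bias needs both a rate that varies with time and person-time that is distributed differently in the two groups. With equal follow-up and a common time zero the null ratio is exactly 1.000. With control follow-up 1.2 to 2 times as long before the data cut-off, it lies between about 0.94 and 1.12 over the assumed trends. The direction depends on whether calendar trend or early clustering dominates. A time-zero mismatch in the subcohort could do more, but only on an assumed reading of an entry rule stated for the exposed alone. The documents give no trend and no control follow-up, so the actual size is unknown. The change is worth making because it is cheap and removes the dependence on these unknowns.

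**What to change.** 1. State the entry rule and time zero for the BMI ≥25 subcohort identically for exposed and unexposed, and reconcile it with the index-date entry in Statistical analysis. Do this first, since time bands cannot be built without it.
2. Split person-time by calendar period (for example 3 to 5 year bands) and by time since entry (for example 0–1, 1–2, 2–5 and over 5 years), and include both in the Poisson model.
3. Optionally, report the SMI rate ratio by calendar period as a secondary result.

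Under the null scenarios above, a model stratified on both time scales returns 1.00 by construction. The cost is record splitting, a few extra parameters and slightly wider intervals. No new data are needed. If the full plan already does this, one sentence under Primary analyses would settle the point.
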